**Treatment Plan:**

Patients with advanced lung cancer complaining of cough lasting for 2 or more weeks will be randomized to receive either pregabalin (at maximal tolerated dose of 300 mg orally daily) (Arm A) or a placebo (Arm B).

Severity of cough will be assessed using Visual Analog Scale (VAS) and Manchester Cough in Lung Cancer Scale (MCLCS). QoL will be assessed using the EORTC QLQ C30 and LC13. VAS, MCLCS and QoL forms will be administered at the time of enrolment in the study, on day 7, and at the end of study visit (9 weeks). Toxicity data will be collected at every visit.

**Duration of Study:** 24 Months

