### 3.6 **Study procedures**

Persons being evaluated for lung cancer in the thoracic medical oncology outpatient department at Tata Memorial Hospital will be questioned about the presence and severity of cough. Patients with cough will be assessed for eligibility. If found eligible and willing to participate in the trial, written informed consent will be obtained. The patient will then be randomized by computer generated blocks to either Arm A (pregabalin 300 mg orally daily) or Arm B (placebo). Investigators, research staff and the patients will be blinded to the study arm. Baseline laboratory tests performed within a week from the date of randomization to assess organ function i.e., complete hemogram, liver and renal function tests and serum electrolytes (sodium, potassium, magnesium, calcium) will be accepted. Evaluation of the performance status and physical examination will be performed by the treating physician. Pulse and blood pressure will be recorded at baseline and every visit.

Information regarding medications that the patient is taking, including additional antitussive medications will be recorded. Plan for oncologic therapy will also be noted.

Tools for assessing cough severity (VAS, MCLCS) will be administered at baseline, on day 7 (+/- 3 days) and 9 weeks (+/- 7 days) from randomization. In patients who are unable to fill out the questionnaires on their own or have trouble reading, the research staff or social workers will help them.

QoL will be assessed using EORCTC QLQ-Q30 and LC13 questionnaires for lung cancer at baseline, day 7 (+/- 3 days) and 9 weeks (+/- 7 days). In patients who are unable to fill out the questionnaires on their own or have trouble reading, the research staff or social workers will help them.

Toxicity data will be recorded and treated as appropriate. The side-effects will be graded according to the Common Terminology Criteria for Adverse Events (CTCAE) v.5. Detailed description of anticipated toxicity and frequency from pregabalin is provided in the next section on adverse events.

- 1. **Adverse events of pregabalin**: In the phase II study evaluating the role of pregabalin and speech pathology combination therapy for patients with chronic refractory cough, the most frequently noted side-effects (all grades) that occurred more commonly with pregabalin as compared to placebo included dizziness (45%), weight gain (25%), blurred vision (20%) and cognitive changes (30%) (13).

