### **4. Adverse Events**

Information about all adverse events will be collected, recorded and followed up as appropriate. Grading of adverse events will be according to CTCAE v.5. An adverse event is any undesirable sign, symptom or medical condition occurring after starting study treatment, even if the event is not considered to be treatment-related.

Medical conditions/diseases present before starting study treatment will be only considered adverse events if they worsen after starting study treatment. Clinical events occurring before starting study treatment but after signing the informed consent form will be recorded on the Case Report Form. Abnormal laboratory values or test results will constitute adverse events only if they induce clinical signs or symptoms or require therapy and will be recorded on the Adverse Events Case Report Form under the signs, symptoms or diagnosis associated with them.

As far as possible, each adverse event will be described by:

1. its duration (start and end dates)
2. the severity grade- as per CTCAE v.5
3. its relationship to the study drug (suspected /not suspected),
4. the action(s) taken.

**4.1 Serious Adverse Event (SAE)**: Information about all serious adverse events will be collected and recorded on the SAE Report Form and will be reported to the independent ethics committee within 24 hours of learning of its occurrence. An SAE is defined in general as an untoward (unfavorable) event which is fatal or life-threatening, required or prolonged hospitalization, significantly or permanently disabling or incapacitating, may jeopardize the subject and may require medical or surgical intervention to prevent one of the outcomes listed above.

Events not considered to be SAEs are hospitalizations occurring under the following circumstances: were planned before entry into the clinical study; are for elective treatment of a condition unrelated to the studied indication or its treatment; occur on an emergency, outpatient basis and do not result in admission (unless fulfilling the criteria above); are part of the normal treatment or monitoring of the studied indication and not associated with any deterioration in condition.

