# **5. Statistical Analysis**

5.1 SAMPLE SIZE CALCULATION: The primary outcome (difference in VAS at baseline and 9 weeks) will used to determine effect size. Sample size will be calculated assuming an effect size of 0.5, with a type I error rate of 5% and power of 80%.

t tests - Means: Difference between two independent means (two groups)

**Input:** Tail(s) = Two

Effect size d = 0.5

α error prob = 0.05

Power (1-β error prob) = 0.80

Allocation ratio N2/N1 = 1

**Output:** Noncentrality parameter δ = 2.828427

Critical t 1.978971

Df = 126

Sample size group A = 64

Sample size group A = 64

Total sample size = 128

Actual power = 0.801460

We will account for a 30% lost-to-follow-up given the fact that a large proportion of patients will have advanced lung cancer. Therefore, the final estimated sample size will be 166.

5.2 STATISTICAL TESTS:

Data will be entered and analyzed using an appropriate statistical program, like SPSS software, version 20 (IBM SPSS Statistics for Windows, Version 20.0. Armonk, NY: IBM Corp.) and R Project for Statistical Computing, version 3.5.1[R Core Team (2013). R: A language and environment for statistical computing. R Foundation for Statistical Computing, Vienna, Austria, URL <http://www.R-project.org/>]*.* Baseline characteristics including demographic data, treatment details, details of the diagnosis and adverse events will be represented as simple percentages.

Statistical Analysis will be done as per intention to treat and per protocol principle. All patients with a complete cough severity assessment at baseline and on 9 weeks will be included for analysis. Patients without any follow-up information after randomization will be excluded. We will use complete-case analysis to handle missing data, i.e. the missing observations will be excluded from the analysis.

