To measure cough severity, the VAS score at 9 weeks will be subtracted from the baseline score. The means of the change from the baseline scores will be calculated for all patients in each arm and the means will be compared between the two arms using two-sided Student’s t-test. A *P* value of <0.05 will be considered significant. The effect size will be determined with the use of Cohen’s d statistic, which is a measure of the difference between two means divided by an estimate of a pooled standard deviation. As per conventional classification, an effect size of 0.2 will be considered small, 0.5 moderate, and 0.8 large (19). A similar methodology will be used to evaluate the cough impact using the MCLCS. The change in the VAS scores and MCLCS scores from baseline to day 7 to 9 weeks and will be explored graphically between the arms.

QoL data will be scored as per the procedure described in the EORTC scoring manual (15,16). Different subdomain wise QoL data will be generated from the QoL dataset. A subdomain wise comparison was performed between the arms, using the linear mixed effect model.

The difference in toxicities between the two arms will be compared using the Pearson chi-square test or Fisher Exact test.

**6. Feasibility of the Study:** We see approximately 1300 lung cancer patients in a year at Tata Memorial Hospital. We expect to complete the study within 24 months of approval of study.

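### The only inclusion rule in section 5.2 requires a complete 9-week cough assessment and is not limited to the cough endpoints, so as worded it can be applied to the toxicity comparison

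*Protocol*

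**What the plan says.** The second paragraph of protocol section 5.2 sets out who is analysed, before any outcome is taken up. It makes four statements in sequence:

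- Both intention to treat and per protocol are named as the principles of analysis.
- The inclusion rule reads "All patients with a complete cough severity assessment at baseline and on 9 weeks will be included for analysis".
- An exclusion follows for anyone who has no information of any kind once randomised.
- Missing data are handled by complete cases, dropping the observations that are missing.

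The sentence just before this paragraph says that baseline characteristics and adverse events will be reported as percentages. The section then goes through the outcomes in turn: cough scores, quality of life, and finally toxicity, where the whole plan is "The difference in toxicities between the two arms will be compared using the Pearson chi-square test or Fisher Exact test".

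On data collection, the synopsis (Treatment Plan) states "Toxicity data will be collected at every visit", and section 4 states "Information about all adverse events will be collected, recorded and followed up as appropriate". Safety is part of the stated aim, and describing adverse effects is a secondary objective.

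**The concern.** A requirement for a 9-week cough score is an efficacy condition. It has no bearing on whether a patient who took study drug had an adverse event. Because the rule stands in the general paragraph and carries no restriction, a programmer following section 5.2 literally would build one set, the week-9 completers, and run every test on it, the toxicity test included. A patient who took the drug, had a recorded toxicity and left in week 3 would then count in neither numerator nor denominator.

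Two things are at stake. The safety comparison would lose patients whose data are already in hand. It would also be made in patients selected by an event after randomisation, staying to week 9, which may depend on tolerability and may do so differently in the two arms.

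**Working it through.** **The plan's own figures.** Section 5.1 assumes d = 0.5, two-sided α = 0.05 and 64 per arm. An exact two-sample t calculation gives noncentrality 2.828, critical t 1.979 and power 0.8015, as printed. The total of 166 is 128 × 1.30 = 166.4. The protocol gives no figure for the toxicity comparison.

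**Inputs.** Randomised: 166, or 83 per arm (1:1, section 5.1). Loss: 30% (section 5.1). Dizziness on pregabalin: 45%, all grades, from the cited cough trial (section 3.6, adverse events of pregabalin). Two inputs are assumptions: the placebo dizziness rate, which the protocol does not give, and the relative risk (RR) of leaving before week 9 for patients with dizziness against those without.

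**Step 1: patients left out if the rule is applied to toxicity.** 166 × 0.70 = 116.2, so about 116 are analysed (58 per arm) and about 50 are not.

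**Step 2: precision, with loss unrelated to side-effects.** The standard error of a difference in proportions grows by √(83/58) = 1.20, so confidence intervals are about 20% wider. Power for 45% against the assumed placebo rate, by the normal approximation with pooled variance under the null:

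| Placebo rate (assumed) | 83 per arm | 58 per arm |
| --- | --- | --- |
| 10% | >99% | 99% |
| 20% | 94% | 83% |
| 25% | 78% | 62% |

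**Step 3: bias, if leaving is related to dizziness.** Hold pregabalin-arm loss at 30%. Let p_n be the probability of leaving without dizziness and p_d = RR × p_n the probability with it.

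- 0.30 = p_n × (0.45 × RR + 0.55), so p_n = 0.30 / (0.45 × RR + 0.55).
- Dizziness rate among completers = 0.45 × (1 − p_d) / 0.70.
- Affected patients not counted = 83 × 0.45 × p_d = 37.35 × p_d.

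| RR | p_n | p_d | Completer rate | Affected, not counted | Excess over RR = 1 |
| --- | --- | --- | --- | --- | --- |
| 1 | 0.300 | 0.300 | 45.0% | 11.2 | 0 |
| 1.5 | 0.245 | 0.367 | 40.7% | 13.7 | 2.5 |
| 2 | 0.207 | 0.414 | 37.7% | 15.5 | 4.3 |
| 3 | 0.158 | 0.474 | 33.8% | 17.7 | 6.5 |

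The last column is the part due to selection. The 11.2 at RR = 1 go uncounted without biasing the rate.

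**Step 4: the opposite direction.** If only 15% of affected patients leave, the completer rate is 0.45 × 0.85 / 0.70 = 54.6%, an overstatement.

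**Step 5: the difference between arms.** With an assumed 20% on placebo and placebo loss unrelated to dizziness, the true difference of 25 points becomes 20.7, 17.7 or 13.8 points at RR = 1.5, 2 or 3.

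**The case against.** The strongest reply is that no sentence places toxicity in the completer set. The rule is worded around the cough assessment. Intention to treat is named just before it. The next sentence expressly excludes only patients with no follow-up at all, which would be redundant if completers were the set for everything. Complete-case handling is by observation, and a recorded adverse event in an early leaver is not a missing observation. A safety population is also commonly defined in an SAP, which is not shown here.

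Much of this stands. A reader might infer that the plan definitely drops early leavers from the safety analysis; the text does not support that, and the absence of a named safety set would be no finding by itself. But the outcome-by-outcome reading is not stated either. The no-follow-up exclusion is just as redundant for the week-9 cough analysis, so it does not show that toxicity has its own set. The point is therefore a rule that the protocol does state, with the wrong scope, and not a missing definition.

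A reader might also infer that pregabalin toxicity will be understated, or that treatment-ending events will vanish. The documents do not establish this. Section 5.1 attributes the 30% loss to advanced disease. The dose-modification text in section 3.6 answers intolerable side-effects with stepwise reduction within the trial. Even where it calls for immediate discontinuation (angioedema, hypersensitivity reactions), nothing says the patient then misses the 9-week assessment. The 45% covers all grades, and mild dizziness need not lead anyone to leave.

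Finally, the point shares a sentence with the handling of missing cough scores. A better method for missing cough scores would still not say who belongs in the toxicity denominator, so that needs its own wording.

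**Conclusion.** The point holds as a fault of scope in a stated rule. As worded, the baseline-plus-week-9 requirement can be applied to toxicity, and at the planned 30% loss that would set aside about 50 of 166 patients together with their adverse event data. The loss of precision follows from that reading alone. The bias does not: it needs leaving to be related to side-effects. Over relative risks of 1 to 3, the pregabalin dizziness rate would read 45% to 34% against a true 45%, and it would read too high if affected patients stayed more often than others. These sizes rest on the cited trial's 45%, equal 30% loss in each arm, and assumed relative risks and placebo rates. They show what could happen and are not a forecast. The matter is worth correcting because safety is part of the aim and the data are already being collected.

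**What to change.** In section 5.2, restrict the requirement for complete baseline and 9-week assessments to the analyses of the cough endpoints. Then add to the toxicity sentence that toxicities are compared in all randomised patients who took at least one dose of study drug, using every recorded adverse event, whether or not the 9-week cough assessment was completed.

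The cost is one or two sentences. Toxicity is already collected at every visit, so no new data are needed, and the design and sample size do not change. If an SAP already defines a safety set in these terms, the protocol sentence should still be narrowed so that the two documents agree.

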# 7. Ethical Considerations

The Investigator or a person designated by him/her will collect informed consent from all participants, prior to which the Investigator or co-investigator must inform each participant of the objectives, benefits, risks and requirements of the study. He/she will also provide the participant with an information sheet in clear, simple language. The study participant will be allowed ample time to inquire about details of the study and to decide whether or not to participate in the study. The study will not commence until approval has been obtained from the Tata Memorial Hospital Human Ethics Committee. The trial will be conducted according to the principles laid down by the International Conference on Harmonization Good Clinical Practice guidelines, the Declaration of Helsinki, Schedule Y (Drugs and Cosmetic Act 1940) and the guidelines established by the Indian Council of Medical Research (ICMR).

# Appendix

1. Side effects of pregabalin
2. Visual Analog scale for Cough

.
[figure not shown]

1. Manchester cough in lung cancer scale

